# Manual acupuncture for the infertile female with polycystic ovary syndrome (PCOS): study protocol for a randomized sham-controlled trial

**DOI:** 10.1186/s13063-019-3667-y

**Published:** 2019-09-11

**Keywords:** Polycystic ovary syndrome, Manual acupuncture, Traditional Chinese Medicine, Infertility, Herb medicine

## Abstract

**Background:**

Polycystic ovary syndrome (PCOS) is one of the most common endocrine diseases for women. Acupuncture is widely used for the infertile female because of it is non-invasive and has fewer side effects, but the powerful evidence for the clinic is still insufficient. Our study intends to explore the effect of manual acupuncture (MA) in the infertile female with PCOS.

**Methods:**

This study is a randomized, sham-controlled, patient-and assessor-blinded trial and aims to evaluate the effect of MA in women with PCOS and infertility. We will recruit 86 women aged 20–40 years with a diagnosis of infertility with PCOS. Participants will be randomly allocated in a 1:1 ratio to the MA group and the sham acupuncture (SA) group. Both groups will receive real herbal medicine treatment as a basic treatment twice a day for three menstrual cycles, the MA group receive real acupuncture treatment and the SA group received placebo acupuncture treatment (non-penetrating). All patients will receive acupuncture treatment twice per week for three menstrual cycles. The primary outcome is pregnancy rate and secondary outcomes include ovulation rate, sex hormones, insulin resistance index (IRI), PCOS symptoms, and Traditional Chinese Medicine (TCM) syndrome scores. Outcome measures will be collected at baseline, each menstrual cycle, the end of treatments, and six months after the last acupuncture treatment. The present protocol followed the SPIRIT guidelines and fulfilled the SPIRIT checklist.

**Discussion:**

This study will be conducted to compare the efficacy of MA versus SA. This trial will help to evaluate whether MA is effective in increasing pregnancy and ovulation rates of the infertile female with polycystic ovary syndrome.

**Trial registration:**

Chinese Clinical Trial Registry, ChiCTR1800014997. Registered on 27 February 2018.

**Electronic supplementary material:**

The online version of this article (10.1186/s13063-019-3667-y) contains supplementary material, which is available to authorized users.

## Background

Polycystic ovary syndrome (PCOS) is one of the most common endocrine diseases for women. Diagnosis is based on two of the following three findings: (1) oligo- and/or anovulation; (2) clinical and/or biochemical signs of hyperandrogenism; and (3) polycystic ovaries and exclusion of other etiologies [1]. The prevalence of PCOS under the Rotterdam criteria was 19.9% in 392 women aged 18–45 years [2]. It is one of the main causes of infertility in women during the reproductive period. PCOS causes > 75% of causes of anovulatory infertility [3].

Clomiphene citrate (CC) is the first-line treatment in anovulatory subfertility patients with PCOS. Gonadotrophins such as follicle-stimulating hormone (FSH) are, in addition to surgery, second-line treatments [4]. The cumulative ovulation rate of CC is as high as 90%, with a pregnancy rate of 50–70%, but the multiple pregnancy rate is up to 15% and rate of ovarian hyper-stimulation syndrome (OHSS) is 2% [5]. Meanwhile, it also has other impact effects [6] such as reversible ovarian enlargement (> 10%), visual symptoms, headaches, etc. Some studies [7, 8] reported that there were several associations between use of CC and birth defects.

Acupuncture and Traditional Chinese Medicine (TCM) methods have a long history of use for gynecological diseases [9] and the related research has increased in the past 20 years [10]. A prevalence study [11] reported that 29% of 428 infertile couples in eight community and academic infertility practices had used a complementary and alternative medicine (CAM) treatment for infertility, 22% had tried acupuncture, and 17% had tried herbal therapy. A review [12] investigated whether utility of TCM would be a feasible method to improve the outcome of female infertility treatment because of inadequate evidence. A meta-analysis [13] demonstrated that co-treatment with TCM and letrozole was more effective than letrozole monotherapy in the treatment of PCOS. Yanjing et al. [14] found that Chinese herbal formula combined with Electroacupuncture (EA) can remarkably improve the menstrual cycle, reduces body weight and the levels of luteinizing hormone (LH), LH/ follicle-stimulating hormone (FSH), total testosterone (T), anti-Mullerian hormone (AMH), improve ovulation, and pregnancy rates. We therefore selected Chinese herbal medicine as a basic treatment.

Recently, a scoping review [15] found that acupuncture had the highest level of evidence for its use among 12 different CAM methods in improving fertility outcomes although this evidence is inconclusive. Some evidence [16, 17] indicated that acupuncture was probably an effective treatments for PCOS, which can improve patients’ clinical symptoms, sex hormone levels, and menstrual cycle and effectively shorten reproduction cycles in infertility patients with PCOS. A systematic review [18] showed that acupuncture can be used to regulate menstruation, assist conception in women, and not increase the risk of multiple pregnancies, but the evidence is insufficient. There is a close relationship between the arrival of qi and therapeutic outcome. As *The Yellow Emperor*’*s Inner Classic: The Spiritual Pivot-The Nine Kinds of Needles and the Twelve Source Points* [19] states: “The most important thing in acupuncture is to get the acupuncture feeling, when it appears, the curative effect will appear.” We therefore use manual acupuncture (MA) to obtain the qi sensation (acupuncture feeling) to get the curative effect.

Nevertheless, Pastore et al. [20] also claimed that both true acupuncture (TA) and sham acupuncture (SA) had a similar improvement in their LH/FSH ratio for these women with PCOS. A randomized clinical trial [21] did not support acupuncture as an infertility treatment in such women. The conclusion of the multicenter-large sample study [22] was potentially incorrect because it had serious flaws. Indeed, the evidence for the effect of acupuncture in the treatment for infertile women with PCOS is still insufficient. Therefore, this study aims to investigate the clinical effectiveness of acupuncture in infertile women with PCOS. Our hypothesis is that MA will regulate the menstrual cycle and improve the ovulation and pregnancy rates.

## Methods/design

### Study design

This is a randomized, sham-controlled, patient-and assessor-blinded trial. A target sample of 86 participants will be recruited from the gynecology clinic at Shuguang Hospital. The flow chart is shown in Fig. 1. The present protocol followed the SPIRIT guidelines and fulfilled the SPIRIT checklist (Additional file 1). The trial protocol is in accordance with the principles of the Declaration of Helsinki and has been approved by Institution review board (IRB) of Shuguang Hospital (the Affiliated Hospital of Shanghai University of TCM) (approval no. 2017–569–52-01). This trial was registered at the Chinese Clinical Trial Registry (ChiCTR1800014997). Any changes that need to be made in the trial protocol will be communicated to all investigators, the ethics committees, and the trial registry. Written informed consent will be obtained from each participant.

**Fig. 1 Fig1:**
[figure not shown]
Study flow chart

### Sample size, randomization, and blinding

Due to the lack of sufficient preliminary studies, it is difficult to determine adequate sample size. According to the studies [23, 24], we hypothesize that the pregnancy rate after MA is 76% and the pregnancy rate after SA is 40%. The calculation equation we used was α = 0.05, 1-β = 0.80 and we determined that a sample size of 36 patients in each group would be sufficient to detect the statistical difference between the two groups, allowing for a 20% withdrawal rate. We will plan to enroll a total of 86 participants with 43 participants in each group. According to the random number sequence generated by Excel, the patients will be randomly divided into either the MA group or the SA group in a 1:1 ratio. We set the blind code in the case for remaining blind when the patients have the adverse effects. The random code and blind code will be conducted by a “third party” independent of the study using opaque envelopes. The envelopes will be sealed and shuffled and the assignment records will not be disclosed until the end of the study. Trial participants, formula doctor, outcome assessors, and data analysts will be blinded to the treatment allocation to minimize potential sources of bias. Because of the special nature of acupuncture, only acupuncturists will not be blinded to the treatment allocation.

### Inclusion criteria

Participants who meet all the following requirements will be allowed for enrollment:
Women aged 20–40 years.Patients who meet the diagnostic criteria for both infertility and PCOS:
Patients who meet the diagnosis of PCOS defined by the Rotterdam criteria proposed in 2003 [1]:
Oligomenorrhea or amenorrhea: oligomenorrhoea is defined as an intermenstrual interval > 35 days or < 8 menstrual bleedings in the past year. Amenorrhea is defined as complete cessation of menstrual cycles for six months or more when a patient has previously had regular cycles and for 12 months or more when the patient has had irregular cycles;Clinical or biochemical hyperandrogenism: biochemical hyperandrogenemia is defined as a total serum testosterone concentration > 60 ng/ dL and clinical hyperandrogenism is defined as a Ferriman-Gallwey (FG) score ≥ 5 in mainland China;Polycystic ovary morphology: this is defined as ≥ 12 antral follicles (2–9 mm in diameter) or an ovarian volume > 10 mL on transvaginal scanning;Patients who meet the diagnosis of infertility [25]: women who fail to achieve a clinical pregnancy after 12 months or more of regular unprotected sexual intercourse; this includes secondary infertility which is failure to conceive after a previous pregnancy.Husband’s semen examination is normal.Willingness to sign the consent form.

### Exclusion criteria

Participants meeting any of the following criteria will be excluded:
Hyperprolactinemia, adrenal or ovarian tumors secreting abnormal increase of androgen, thyroid disease, suspected Cushing syndrome, and other heart and kidney diseases.Those who had used hormone drugs such as estrogen or oral contraceptives in the last month.Those who had used other drugs that affect reproductive function or metabolism (such as anti-obesity drugs, anti-diabetic drugs, etc.) or have participated in other clinical trials in the past two months.Those who had received acupuncture treatment.Those who had other infertility factors (such as tubal blockage, immune infertility, etc.).Those who were unable to cooperate with the completion of the study, including patients with infectious diseases, mental illness, and other medical histories.

### Interventions

Both TA and SA groups will receive acupuncture sessions for a total of three menstrual cycles. All the patients will receive herbal medicine twice a day for three menstrual cycles. The same doctor (the professor of obstetrics and gynecology in Shuguang hospital who has 35 years of work experience) will slightly adjust the formula each week depending on the changes in the patients’ symptoms, tongue coating, and pulse (main herbal formula components are shown in Table 1). During the menstrual period, patients will be orally administered the *Taohong Siwu* decoction. Non-menstrual period treatment will be based on pattern differentiation: (1) spleen–kidney Yang deficiency will be given *Bushen Tiaojing* decoction; and (2) liver–kidney Yin deficiency will be given *Guishao Dihuang* decoction. Participants will receive all herbs from the same hospital and will be instructed on how to make the decoction.

**Table 1 Tab1:** Main herbal formula selection

Period	Pattern	Formula	Composition
Menstrual period		*Taohong Siwu* decoction	*Radix Rehmanniae* Preparata, *Radix Angelicae Sinensis*, *Radix Paeoniae Alba*, *Rhizoma Chuanxiong*, *Semen Persicae*, *Flos Carthami*
Non-menstrual period	Spleen–kidney Yang deficiency	*Bushen Tiaojing* decoction	*Radix Angelicae Sinensis*, *Rhizoma Chuanxiong*, *Radix Rehmanniae Preparata*, *Radix Paeoniae Alba*, *Poria*, *Radix Salviae Miltiorrhizae*, *Semen Cuscutae*, *Radix Astragali*, *Fructus Lycii*, *Rhizoma Dioscoreae*
	Liver–kidney Yin deficiency	*Guishao Dihuang* decoction	*Radix Rehmanniae*, *Radix Paeoniae Alba*, *Fructus Lycii*, *Cortex Moutan*, *Rhizoma Anemarrhenae*, *Radix Ginseng*, *Radix Glycyrrhizae*, *Cortex Lycii*

According to the textbook *Acupuncture and Moxibustion* [26], and taking opinions from Chinese acupuncture experts, the essential acupuncture points selected are as follows: RN4 (*Guanyuan*); EX-CA1 (*Zigong*); ST29 (*Guilai*); ST36 (*Zusanli*); and SP6 (*Sanyinjiao*). The additional individualized acupuncture points will be chosen by the practitioners according to the patterns of identification: (1) spleen–kidney Yang deficiency plus RN6 (*Qihai*), RN12 (*Zhongwan*), ST25 (*Tianshu*); and (2) liver–kidney Yin deficiency will add with bilateral KI3 (*Taixi*), KI6 (*Zhaohai*). According to the menstrual cycle, the follicular phase will use the acupuncture points bilateral KI3 (*Taixi*) and KI6 (*Zhaohai*); the ovulatory phase will use the acupuncture points bilateral LR3 (*Taichong*), SP10 (*Xuehai*), PC6 (*Neiguan*), and DU20 (*Baihui*) (Table 2). A placebo device [27] will be applied in both groups for better implementation of blindness. The schematic diagram of acupuncture treatment is shown in Fig. 2. The acupuncture treatment in both groups will take 30 min per session, twice per week, from the third day of menstruation to the third day after ovulation for three menstrual cycles. Acupuncture treatments will be stopped upon a positive pregnancy test. The test will be done on the 14th day after each ovulation.

**Table 2 Tab2:** Acupuncture point selection

Point	Location
RN4 (*Guanyuan*)	On the lower abdomen at the anterior midline, 3 *cun* below the umbilicus
EX-CA1^a^ (*Zigong*)	On the lower abdomen, 4 *cun* below the center of the umbilicus and 3 *cun* lateral to the anterior midline
ST29^a^ (*Guilai*)	1 *cun* cranial to the pubic bone and 2 *cun* lateral of the midline
ST36^a^ (*Zusanli*)	At the anterior aspect of the leg 3 *cun* inferior to ST35 (*Dubi*) on the line connecting ST35 (*Dubi*) to ST41 (*Jiexi*)
SP6^a^ (*Sanyinjiao*)	On the tibial aspect of the leg posterior to the medial border of the tibia, 3 *cun* superior to the prominence of the medial malleolus
Syndrome 1	
RN6 (*Qihai*)	With the patient supine, the point is halfway between the center of the umbilicus and RN4 (G*uan yuan*)
RN12 (*Zhongwan*)	On the upper abdomen at the anterior median line, 4 *cun* above the umbilicus
ST25^a^ (*Tianshu*)	On the upper abdomen 2 *cun* lateral to the center of the umbilicus
Syndrome 2 and phase 1	
KI3^a^ (*Taixi*)	On the posteromedial aspect of the ankle in the depression between the prominence of the medial malleolus and the calcaneal tendon
KI6^a^ (*Zhaohai*)	On the medial aspect of the foot in the depression inferior to the medial malleolus, 1 *cun* inferior to the prominence of the medial malleolus
Phase 2	
LV3^a^ (*Taichong*)	On the dorsum of the foot between the first and second metatarsal bones in the depression distal to the junction of the bases of the two bones and over the dorsalis pedis artery
SP10^a^ (*Xuehai*)	With the knee flexed, on the medial side of the thigh 2 *cun* above the superior medial corner of the patella on the prominence of the medial head of the quadriceps muscle of the thigh
PC6^a^ (*Neiguan*)	On the medial aspect of the forearm between the palmaris longus and the flexor carpi radialis tendons, 2 *cun* proximal to the palmar wrist crease
DU20 (*Baihui*)	On the head at the anterior median line, 5 *cun* superior to the anterior hairline

Based on pattern and phase differentiation, syndrome 1 = Spleen–kidney Yang deficiency; syndrome 2 = Liver–kidney Yin deficiency, phase 1 = follicular phase; phase 2 = ovulatory phase

^a^Bilateral points

**Fig. 2 Fig2:**
[figure not shown]
Schematic diagram of acupuncture device

#### Manual acupuncture group

Disposable, stainless steel needles (0.25 × 40 mm, provided by Wuxi Jiajian Medical Instrument Co. Ltd., China) will be punctured through the device when patients are in the supine position and inserted 10–30 mm deep, depending on location. The needles will be retained for 30 min and manually lifted, thrust, twisted, and rotated moderately every 10 min to maintain the *deqi* sensation. When qi arrives, the acupuncturist will feel tightness around the needle, the patients will feel such sensations as soreness, numbness, distention, and heaviness at the point. These sensations can radiate along the course of the channel.

#### Sham acupuncture group

The procedure and duration of treatment in the SA group will be identical in the TA group except the needles (0.25 × 25 mm, blunt tip, provided by Wuxi Jiajian Medical Instrument Co. Ltd., China) are blunt tip and there will be no skin penetration or manual stimulation.

#### Practitioner background

The TA and SA treatments will be conducted by acupuncturists who are licensed by the Chinese medicine practitioner qualification certificate and who specialize in acupuncture with at least three years of clinic experience. They will have studied acupuncture for > 10 years and graduated from a TCM university. All practitioners will undergo intensive and customized training for a full understanding of the SA procedure and will be trained to administer acupuncture using a sham needle device. The techniques for the entire treatment procedure will be standardized between practitioners.

### Outcome measures

Outcomes will be collected at baseline, each menstruation, after three menstrual cycles of treatment, and follow-up at six months after the completion of the treatment. The overview of the outcome measurement at the different time points is shown in Table 3.

**Table 3 Tab3:** Overview of study visits

	Screening and baseline visit	Menstrual cycles			Six months after the last acupuncture treatment
		1st	2nd	3rd	
General condition ^a^	√				
Gynecological examination	√				
Fasting blood samples for sex hormone ^b^, FINS, FBG, HbA1c	√			√	
Transvaginal ultrasound	√	√	√	√	
Pregnancy test (blood β-HCG)				√	
Treatment record ^c^		√	√	√	
Questionnaire ^d^	√			√	
Telephone follow-up ^e^					√

^a^General condition include age, BMI, menstrual and obstetrical histories

^b^Sex hormones include: E2, T, P, FSH, LH, PRL, DHEAS, SHBG

^c^Treatment record includes date and adverse events

^d^Questionnaire includes the PCOS and TCM syndrome scores

^e^Inquires if the participants were pregnant

*E2* estradiol, *T* total testosterone, *P* progesterone, *FSH* follicle-stimulating hormone, *LH* luteinizing hormone, *PRL* prolactin, *DHEAS* dehydroepiandrosterone sulfate, *SHBG* sex hormone-binding globulin, *BMI* body mass index, *FINS* fasting insulin, *FBG* fasting blood-glucose, *HbA1c* glycated hemoglobin

#### Primary outcome

The primary outcome is the pregnancy rate during the trial, including ectopic pregnancy. Blood β-HCG will be measured at 14 days after ovulation.

#### Secondary outcome

##### Ovulation rate

Ovulation will be observed through Basal body temperature (BBT) or B ultrasound every menstrual cycle. From the 10th day of the menstrual period, the patients will receive B ultrasound 3–4 times to observe the size of the follicle and whether it has discharged.

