### Data analysis

All statistical analyses of the data will be performed using SPSS program V.21.0 (SPSS Inc., Chicago, IL, USA). A *P* value < 0.05 will be considered statistically significant. For cases in which we do not finish all the treatment, we select intention-to-treat (ITT) analysis to avoid the effects of crossover and drop-out. Measured data will be expressed as mean ± SD ($$ \overline{x} $$ ±s) if it obeys a normal distribution or approximate normal distribution. Median (interquartile range [IQR]) will be used if the data do not obey the normal distribution and count data will be expressed in terms of the number of cases. We will use chi-square tests for categorical data and two-sample t-test or Wilcoxon rank sum test for continuous data, according to whether the data are normally distributed. The variance analysis will be performed for the difference between the two groups and within the group. The stratified analysis will be performed to control the confounding factor if necessary. Data analysis will be conducted by statisticians who are independent of the research team.

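### The unit of the ovulation rate is not fixed; if it is taken per cycle and cycles are pooled, the named chi-square test ignores repeated cycles within a woman and is biased by stopping at conception

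*Protocol article*

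**What the plan says.** Under Ovulation rate, the protocol article states: "Ovulation will be observed through Basal body temperature (BBT) or B ultrasound every menstrual cycle". Interventions sets the number of cycles: "Both TA and SA groups will receive acupuncture sessions for a total of three menstrual cycles". Table 3 schedules transvaginal ultrasound in each of the three. A woman can therefore give up to three yes/no ovulation results.

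Interventions also states "Acupuncture treatments will be stopped upon a positive pregnancy test" and, of the pregnancy test, "The test will be done on the 14th day after each ovulation". Conception can therefore end a woman's series of ovulation observations after cycle 1 or 2.

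Data analysis says "We will use chi-square tests for categorical data and two-sample t-test or Wilcoxon rank sum test for continuous data". It adds two general provisions: "The variance analysis will be performed for the difference between the two groups and within the group" and "The stratified analysis will be performed to control the confounding factor if necessary". Neither is tied to a named outcome.

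The Abstract lists ovulation rate among the secondary outcomes, and the hypothesis at the end of the Background includes it. No numerator, denominator or unit is given for it.

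**The concern.** The text permits two readings. Per woman (ovulated at least once), each woman counts once and chi-square is appropriate. Per cycle, with cycles pooled, two things go wrong.

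- **Clustering.** Cycles from one woman are likely to resemble each other. Chi-square on pooled cycles then uses too small a standard error.
- **Selective stopping.** Women who ovulate readily conceive sooner and drop out of the later-cycle denominator, while poor ovulators stay for all three cycles. The arm with more pregnancies loses more good ovulators, so its per-cycle rate falls even if the treatment does nothing to ovulation.

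If MA raised pregnancy as the trial expects, a pooled analysis could show more pregnancies beside apparently worse ovulation, purely as an artefact.

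**Working it through.** The protocol states no figure for ovulation, so there is none to reproduce.

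**Inputs from the protocol:** 43 women per arm; up to 3 cycles each (43 × 3 = 129 per arm); assumed pregnancy rates of 76% (MA) and 40% (sham acupuncture, SA).

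**Assumptions (not in the protocol):** mean per-cycle ovulation probability; within-woman correlation ρ; each woman's own ovulation probability p follows a beta distribution; within an arm, each ovulation leads to conception with a constant probability c, chosen to give the arm's pregnancy rate.

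**Step 1: clustering alone, no stopping.** The design effect is 1 + (3 − 1)ρ = 1 + 2ρ. The true size of a nominal 5% test is about 2[1 − Φ(1.96/√(1 + 2ρ))].

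| ρ | Design effect | Formula | Simulated, mean 0.6 |
|---|---|---|---|
| 0 | 1.0 | 5.0% | 5.1% |
| 0.1 | 1.2 | 7.4% | 7.0% |
| 0.3 | 1.6 | 12.1% | 12.3% |
| 0.5 | 2.0 | 16.6% | 16.8% |

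The simulations used 20,000 replicates per scenario. Means of 0.5 and 0.7 give much the same values.

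**Step 2: stopping at conception, identical true ovulation in both arms.** Worked example with mean 0.6 and ρ = 0.3. The beta parameters sum to 1/0.3 − 1 = 2.333, so they are 1.4 and 0.933. Then:

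- E[p] = 0.6
- E[p²] = 0.6 × 2.4/3.333 = 0.432
- E[p³] = 0.432 × 3.4/4.333 = 0.339

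Expected cycles per woman: 1 + (1 − cE[p]) + (1 − 2cE[p] + c²E[p²]).

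Expected ovulations per woman: E[p] + (E[p] − cE[p²]) + (E[p] − 2cE[p²] + c²E[p³]).

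- MA, c = 0.74: cycles = 1 + 0.556 + 0.349 = 1.905 (81.9 for 43 women). Ovulations = 0.600 + 0.280 + 0.146 = 1.027. Pooled rate = 1.027/1.905 = 0.539. Check: pregnancies = 0.74 × 1.027 = 0.76.
- SA, c = 0.27: cycles = 1 + 0.838 + 0.707 = 2.545 (109.5 for 43 women). Ovulations = 0.600 + 0.483 + 0.391 = 1.475. Pooled rate = 1.475/2.545 = 0.579. Check: pregnancies = 0.27 × 1.475 = 0.40.

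The false deficit for MA is 0.579 − 0.539 = 0.040. Simulation gives the same rates, and across ρ at mean 0.6:

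| ρ | MA v SA pooled rate | False deficit | Falsely significant in favour of SA (nominal 2.5%) |
|---|---|---|---|
| 0 | 0.600 v 0.600 | 0 | 2.6% |
| 0.1 | 0.582 v 0.593 | 1 point | 4.3% |
| 0.3 | 0.539 v 0.579 | 4 points | 12.1% |
| 0.5 | 0.473 v 0.565 | 9 points | 28.4% |

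Milder settings:

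- Mean 0.8: 0.771 v 0.790 at ρ = 0.3, and 0.749 v 0.782 at ρ = 0.5 (2 to 3 points).
- Mean 0.6 with pregnancies of 50% v 30%: 0.572 v 0.585 at ρ = 0.3, and 0.550 v 0.575 at ρ = 0.5 (about 1 to 3 points).

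**Step 3: per woman.** A woman who conceives has already ovulated, so stopping removes nothing. At mean 0.6 and ρ = 0.3, P(never ovulates in three cycles) = (0.933 × 1.933 × 2.933)/(2.333 × 3.333 × 4.333) = 0.157. The expected proportion is therefore 0.843 in both arms, whatever the pregnancy rates. Simulated type I error of chi-square is at most about 6% in every scenario, and well below 5% when nearly all women ovulate.

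**The case against.** The strongest reply is that the protocol nowhere says that the rate is per cycle or that cycles are pooled. Observing each cycle is a monitoring schedule, not a denominator, and the per-woman reading fits the same sentences with neither problem. A reader might infer that the plan commits to an invalid test with type I error well above 5%. The text does not support that, and the inflation holds only under the pooled reading with appreciable correlation. The Background calls a clomiphene figure cumulative and the outcome heading does not use that word, but this settles nothing either way.

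Three further points stand in part.

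- A reader might infer that women leave the trial on conceiving. The text stops only acupuncture, and the analysis is intention-to-treat. A pregnant woman nevertheless yields no further ovulation observations, which is all the argument needs.
- Chi-square is not the only analysis named. Variance analysis and stratified analysis are also mentioned, but neither clearly handles repeated binary data.
- The largest figure is strained. At mean 0.6 and ρ = 0.5 only 0.776 of women ever ovulate, so 76% pregnant means 0.76/0.776 = 98% of them conceive within three cycles.

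It can also be said that a denominator is a detail an article may leave to the full protocol or analysis plan. As a bare omission it would not be worth raising. Here, however, the article itself fixes the schedule, the event that truncates it and the test, and together these permit a biased result.

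**Conclusion.** The point holds as a conditional one. The unit of the ovulation rate is open, and one of the two readings that the text allows is invalid under the only test named for categorical data. On that reading, type I error runs from about 5% with no correlation to about 17% at 0.5. At mean ovulation 0.6 and the protocol's own pregnancy rates, the false deficit for MA runs from 0 to 9 points. It is smaller with higher mean ovulation or a smaller pregnancy difference, and zero if women do not differ in their ovulation probability. Some variation is plausible, since the eligibility criteria span oligomenorrhoea to amenorrhoea and need only two of three diagnostic features, but its size is undocumented.

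The selection bias runs against MA, so it would not by itself create a false claim for MA. The outcome is secondary, and the primary outcome and sample size are untouched. This is an inexpensive improvement worth making, not a fault in the main analysis.

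**What to change.** Define the ovulation outcome per randomised woman: ovulated at least once in the three treatment cycles, with conception counted as ovulation. Test it by chi-square.

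If a per-cycle rate is also reported, analyse it with a logistic GEE or mixed model with woman as the cluster, and label it as conditional on not yet being pregnant. The label matters because allowing for clustering repairs the standard error but does not by itself remove the selection caused by conception.

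The cost is about two sentences in the outcome and analysis sections, with the same data. The small downside is that the per-woman proportion uses less of the cycle information and has a ceiling when nearly all women ovulate.
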